### **Definitions**

#### **Adverse Event**

Generally, an adverse event is any untoward medical occurrence in a subject who has received an investigational intervention.

Specific to this study, as noted above, common complications of prematurity will be collected and analyzed as secondary outcomes.

Adverse events judged to be related to being in the VentFirst study will be considered for AE reporting, as below.

#### **Expectedness**

The expectedness of the adverse event will be determined by the Investigator based on current literature and the Investigator's experience. We have included in this study adverse events that have been found to be related to the delayed cord clamping intervention in previous studies (see section 6). In addition, we have required the investigator to report any other unanticipated AEs that he/she feels may have been related to the intervention.

### Severity

Where applicable, severity of adverse events can be described as indicated in the following table:

**Table 2.** Adverse Event Severity Grading Scale

| Grade | Severity                                                                                                                                                                                                                                                                                        |
|-------|-------------------------------------------------------------------------------------------------------------------------------------------------------------------------------------------------------------------------------------------------------------------------------------------------|
| 1     | Mild: transient symptoms, only requiring monitoring or symptomatic treatment and clinically significant                                                                                                                                                                                         |
| 2     | Moderate: illness or condition which requires new or significantly altered specific therapy                                                                                                                                                                                                     |
| 3     | Severe: illness or condition unresponsive to medical therapy                                                                                                                                                                                                                                    |
| 4     | Life-threatening: illness or condition complicated by acute life-threatening metabolic or cardiovascular complications (e.g., circulatory failure, hemorrhage, sepsis); life-threatening physiological consequences; or need for intensive or emergent invasive procedure (e.g., major surgery) |
| 5     | Death                                                                                                                                                                                                                                                                                           |

### Attribution Assessment (Relatedness)

The site principal investigator, or qualified designee, will evaluate all AEs and assess their relatedness, if any, to the study intervention. The following criteria will be used to define relatedness:

#### Related encompasses:

**Definite:** Direct association between AE and the study intervention

**Probable:** AE more likely explained by the study intervention

**Possible:** Study intervention and other cause could explain the AE equally well. (Can't rule either out)

**Not related:** AE clearly explained by another cause, requires other cause to be documented in the medical record.

### Reportable Adverse Events

The adverse events listed below may be related to the subject being in the study and are the only adverse events that will require reporting.

| Adverse Event                                                                                            | Timing                               |
|----------------------------------------------------------------------------------------------------------|--------------------------------------|
| Mother                                                                                            |                                      |
| Delivery-related infection                                                                               | Prior to discharge                   |
| Retained placenta                                                                                        |                                      |
| Other adverse events deemed by site PI to be definitely or probably related to being in the study | Any time                             |
| Infant                                                                                            |                                      |
| Hypothermia <36°C on admission to NICU                                                                   | NICU admission                       |
| Medication given for low blood pressure                                                                  | 1 st 24 hours after birth |
| Anemia: hematocrit <30% (Hgb < 10 g/dl)                                                                  | 1 st 24 hours after birth |
| Polycythemia: hematocrit >65% (Hgb > 22 g/dl)                                                            | 1 st 24 hours after birth |
| Bilirubin >12 mg/dl                                                                                      | 1 st 10 days after birth  |
| IVH grade 1-2                                                                                            | prior to 36 weeks PMA                |
|                                                                                                          |                                      |
| Cystic periventricular leukomalacia                                                                      | prior to 36 weeks PMA                |
| Necrotizing Enterocolitis (Modified Bell's stage 2-3)                                                    | prior to 36 weeks PMA                |
| Other adverse events deemed by site PI to be definitely or probably related to being in the study | Any time                             |

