## 5 EVALUATIONS AND ASSESSMENTS

### Time and Events Table

**Table 1: SCHEDULE OF EVENTS**

| Assessments / Procedures              | Pre-Study | Day 1 (Birth Day) | Follow-Up 1 st 24h | HUS at 7-10 days | Follow-Up 1 st 10 days | Final HUS 36 wks PMA +/- 7days | Follow-up 36 wks PMA  +/- 7 days | Follow-Up 18-24 months CGA |
|---------------------------------------|-----------|-------------------|-------------------------------|------------------|-----------------------------------|--------------------------------|----------------------------------------------|----------------------------|
| Review inclusion/exclusion criteria   | X         |                   |                               |                  |                                   |                                |                                              |                            |
| Obtain Informed Consent               | X         |                   |                               |                  |                                   |                                |                                              |                            |
| Medical history                       | X         |                   |                               |                  |                                   |                                |                                              |                            |
| Confirm eligibility       |           | X                 |                               |                  |                                   |                                |                                              |                            |
| Randomization                         |           | X                 |                               |                  |                                   |                                |                                              |                            |
| Vent First Study intervention         |           | X                 |                               |                  |                                   |                                |                                              |                            |

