## 6 OUTCOME MEASURES

All outcomes measures will be part of routine care and recorded in the medical record, with the exception of outside expert readings of HUS at 7-10 days and last HUS at birth hospital prior to 36 weeks.

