### **Specification of the Appropriate Outcome Measures**

Multiple head ultrasounds are performed as routine care for all EPT infants. At each site, HUS will be performed 7-10 days after birth (nearly all IVH occurs before this time), and this will be used for primary outcome assessment. Failure to obtain a 7-10 day HUS will be considered as a protocol deviation, and the subsequent HUS accepted for the purposes of determining the primary outcome as discussed in section 7 on statistics.

The HUS performed at the birth hospital closest to the 36 week PMA follow-up time point will be used for the secondary HUS outcome assessment. The primary reason for the late HUS is to evaluate for cystic periventricular leukomalacia, which is usually not present on the 7-10 day HUS but can be associated with adverse perinatal and birth events and is associated with adverse long-term neurologic outcomes. The final HUS is also important for assessing post-hemorrhagic hydrocephalus, which evolves over time and is associated with severe (Grade III-IV) IVH and adverse long-term neurologic outcomes. If a center performs brain MRI rather than HUS near 36 weeks PMA, this will be used for secondary outcomes assessment.

**For clinical care and for adverse event reporting**, all HUS's will be read per standard of care by board-certified pediatric radiologists trained in neonatal HUS interpretation at each study site. These reports will not be used for primary or secondary study outcomes assessment.

**For study endpoints**, an independent radiologist at non-study institutions (blinded to study assignment) will independently read the 7-10 day and the final 36 week PMA HUS on each study infant. These readings will be performed in batch at intervals to be determined by the statistical analysis plan and DSMC requirements. Any HUS with discrepant findings between the local and the independent radiologist that would impact primary outcome assessment will be evaluated by another independent radiologist.

Quality review of each HUS will be performed by board-certified pediatric radiologists trained in neonatal HUS interpretation at each study site. If

studies are judged to be of poor quality for standard interpretation, they will be repeated as part of routine clinical care.

Detailed instructions regarding transmitting images to the independent radiologists, details of the HUS central reading center process, and HUS quality assurance can be found in the study MOP.

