## **8 ADVERSE EVENTS AND REPORTING**

Extremely preterm infants commonly have multiple clinical complications and laboratory abnormalities associated with prematurity, and those listed in section 6 will be collected and analyzed as secondary outcomes. These outcomes will be collected in the MuSIC database at times indicated in the MOP and reviewed monthly by the UVA Study Team. The DSMC will receive regular reports of secondary outcomes and compare rates in infants in the two study arms and compare overall rates in study infants to reported rates for EPT infants at NICUs in the Vermont Oxford Network or similar databases. If there is a significant imbalance of secondary outcome rates between the study arms or compared to current EPT rates, the proper course of action will be discussed by the study PIs and the DSMC.

Adverse events deemed related (definitely, probably or possibly) to a mother or infant being in the study will be collected and reported, as defined below. Recording of such adverse events will start at the time of the study intervention (birth) and will stop at the time of hospital discharge after delivery for mothers and at discharge home or 36 weeks PMA for infants. Any adverse events not resolved at the time a subject goes off study will be recorded as 'ongoing'.

Adverse events must be assessed for expectedness, severity, attribution (relatedness to the study intervention), and seriousness by the site Investigator, or another qualified study team member.

Adverse events deemed related to the intervention must be reported as SAEs if they become serious.

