### Reportable Serious Adverse Events

Generally, a serious adverse event is one that is temporally associated with the subject's participation in a research study that results in death or disability, is life-threatening, or prolongs hospitalization. Many of the typical complications of prematurity fit this description and only the following SAEs possibly related to the study will be reported as such.

| Serious Adverse Event                                                                                     | Timing                                                               |
|-----------------------------------------------------------------------------------------------------------|----------------------------------------------------------------------|
| Mother                                                                                             |                                                                      |
| Any condition leading to death                                                                            | Prior to discharge                                                   |
| Post-partum hemorrhage $\geq$ 1000 mL                                                                     | In the first 24h after delivery (including delivery room blood loss) |
| Serious unexpected adverse event judged to be definitely or probably related to being in the study | Any time                                                             |
| Infant                                                                                             |                                                                      |
| Any condition leading to death                                                                            | Prior to 36 wks PMA                                                  |
| Chest compressions or epinephrine in DR                                                                   | In the delivery room                                                 |
| IVH grade 3-4                                                                                             | On 7-10 day HUS or 36 week PMA HUS                                   |
| Cerebellar hemorrhage                                                                                     | On 7-10 day HUS or 36 week PMA HUS                                   |

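### Cystic PVL stops being a reportable adverse event at 36 weeks PMA, but the scan meant to find it may be done up to 7 days later

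*Protocol*

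**What the plan says.** Section 8, Reportable Adverse Events, limits both cystic PVL and IVH grade 1-2 to "prior to 36 weeks PMA". It says that the listed events "are the only adverse events that will require reporting". The opening of Section 8 stops adverse event recording "at discharge home or 36 weeks PMA for infants". Subject Status Definitions in Section 4 takes the infant off study at 36 weeks PMA, discharge home or death, whichever is first.

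Table 1 in Section 5 has a column headed "Final HUS 36 wks PMA +/- 7days" with adverse event reporting marked in it. The footnote to that row refers the reader to Section 8.

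Section 6, Specification of the Appropriate Outcome Measures, states: "The primary reason for the late HUS is to evaluate for cystic periventricular leukomalacia". It adds that this lesion is usually absent at 7-10 days, and it chooses the late scan by proximity: "The HUS performed at the birth hospital closest to the 36 week PMA follow-up time point will be used". The opening sentence of Section 6 describes the late scan differently, as the "last HUS at birth hospital prior to 36 weeks".

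In the serious adverse event table of Section 8, grade 3-4 IVH and cerebellar hemorrhage carry the timing "On 7-10 day HUS or 36 week PMA HUS". That timing is tied to a scan and not to a date.

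**The concern.** Cystic PVL is the listed event that depends most on the late scan. Under the present wording, its status as a reportable adverse event turns on whether a site scans a few days before or a few days after 36w0d, although both are compliant. Section 6 (Safety) and Section 7 rely on comparing reportable events by arm and tabulating them by arm and cohort. A cut-off inside the scan window can make that tabulation incomplete. It can also make capture uneven across sites, because some may follow the mark in Table 1 and others the cut-off in Section 8.

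The stop date causes a second conflict. The serious adverse event table expects findings from the 36-week scan to be reported, but for a scan on or after 36w0d the general rule has already closed recording.

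**Working it through.** The protocol gives no figure for this point, so the check compares time windows.

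**Inputs**
- Final scan window: 36w0d ± 7 days (Section 5, Table 1).
- Reporting limit for cystic PVL and IVH grade 1-2: before 36w0d (Section 8, Reportable Adverse Events).
- End of infant recording and of study status: 36w0d if not earlier (Section 8 opening; Section 4).

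**Days**
- Permitted scan days: 35w0d to 37w0d, 7 + 1 + 7 = 15.
- Days that meet the reporting limit: 35w0d to 35w6d, 7.
- Days inside the scan window but outside the limit: 36w0d to 37w0d, 15 − 7 = 8.

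**One compliant scan at 36w3d, read literally**

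| Finding first seen | Event table | Section 8 stop date |
|---|---|---|
| Cystic PVL | Outside its row | Recording closed |
| IVH grade 1-2 | Outside its row | Recording closed |
| Cerebellar hemorrhage | Inside its row | Recording closed |
| IVH grade 3-4 | Inside its row | Recording closed |

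The first two rows are consistently not reportable. The last two contradict themselves: the table asks for a report and the stop date has passed.

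**Does other text close the gap?**
- The adverse event mark in Table 1 at the final scan shows intent, but its footnote defers to Section 8, which contains the cut-off.
- The catch-all row for other events at any time requires the site investigator to judge the event definitely or probably related. That is not routine capture.
- The opening of Section 6 would bring the late scan before 36 weeks and largely remove the gap. It conflicts with Table 1 and with the proximity rule later in Section 6.

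**After alignment**, with the two rows and the stop date tied to the final scan, all 15 permitted days are covered.

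The 8 of 15 is a share of days, not of infants or cases. The protocol gives no distribution of scan dates and no PVL rate.

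**The case against.** The strongest reply is that little information is lost. Cystic PVL is a component of the secondary severe brain injury composite, which Section 6 defines on the early or late scan, and it is also a tertiary outcome. Section 8 has the DSMC receive secondary outcomes and compare them by arm. This stands. A reader might infer that late PVL cases never reach the DSMC, but the documents do not support that, because they arrive within the composite.

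A reader might also infer that the composite itself loses these cases, since it sits under a heading that runs to 36 weeks PMA. The specific definitions, by scan and by proximity to 36 weeks, are better evidence of what is meant than the heading.

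A third tempting step is to turn 8 of 15 days into a fraction or number of missed cases. That would need evenly spread scan dates, an assumed PVL rate and an assumed number of scanned survivors. It would also ignore that multiple scans are routine, so that some PVL is seen, and is reportable, before 36 weeks.

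Nor is bias between arms shown. Scan timing is plausibly a matter of site practice, and randomization is stratified within site. IVH grade 1-2 is barely affected, because Section 6 says that nearly all IVH occurs before the 7-10 day scan.

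Finally, Table 1 suggests that reporting at the final scan was intended. That is a fair reading of intent, but the text that governs reporting says otherwise.

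**Conclusion.** The inconsistency is real and its impact is modest. Taken literally, Section 8 leaves cystic PVL first seen on 8 of the 15 permitted final-scan days outside adverse event reporting, and its stop date contradicts its own serious adverse event rows for scans on those days. The consequence is a possible under-count of PVL in the adverse event tabulation and uneven capture across sites.

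The primary endpoint, the sample size, the interim boundaries and the composite definition are unaffected. The conclusion assumes that Table 1 and the proximity rule in Section 6 define the late scan. If the opening sentence of Section 6 governed instead, the gap would mostly disappear, but those two places would then be wrong.

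**What to change.** 1. In the reportable adverse event table, replace the timing for cystic PVL and IVH grade 1-2 with scan-based wording like that of the serious adverse event table: any head ultrasound up to and including the final 36-week scan, with its ± 7 day window.
2. In the opening of Section 8 and in Subject Status Definitions, end infant adverse event recording and study status at the later of 36 weeks PMA and the final scan for infants still in hospital. Leave discharge home and death as they are.
3. Reconcile the opening sentence of Section 6 with Table 1 and with the proximity rule, so that the late scan has one definition.

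The composite definition needs no change. The cost is an edit to two table rows and three sentences, with recording open at most 7 days longer per infant. No scan, visit or procedure is added.

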### Reportable Serious Adverse Events

Generally, a serious adverse event is one that is temporally associated with the subject's participation in a research study that results in death or disability, is life-threatening, or prolongs hospitalization. Many of the typical complications of prematurity fit this description and only the following SAEs possibly related to the study will be reported as such.

| Serious Adverse Event                                                                                     | Timing                                                               |
|-----------------------------------------------------------------------------------------------------------|----------------------------------------------------------------------|
| Mother                                                                                             |                                                                      |
| Any condition leading to death                                                                            | Prior to discharge                                                   |
| Post-partum hemorrhage $\geq$ 1000 mL                                                                     | In the first 24h after delivery (including delivery room blood loss) |
| Serious unexpected adverse event judged to be definitely or probably related to being in the study | Any time                                                             |
| Infant                                                                                             |                                                                      |
| Any condition leading to death                                                                            | Prior to 36 wks PMA                                                  |
| Chest compressions or epinephrine in DR                                                                   | In the delivery room                                                 |
| IVH grade 3-4                                                                                             | On 7-10 day HUS or 36 week PMA HUS                                   |
| Cerebellar hemorrhage                                                                                     | On 7-10 day HUS or 36 week PMA HUS                                   |
| Pneumothorax requiring intervention                                                                       | 1 st 24 hours after birth                                 |
| Exchange transfusion for hyperbilirubinemia                                                               | 1 st 10 days after birth                                  |
| Serious unexpected adverse event judged to be definitely or probably related to being in the study | Any time                                                             |

